## Abstract

**Background:**

Low mood is a common mental health problem with significant health consequences. Studies have shown that cognitive behavioural therapy (CBT) is an effective treatment for low mood and anxiety when delivered one-to-one by an expert practitioner. However, access to this talking therapy is often limited and waiting lists can be long, although a range of low-intensity interventions that can increase access to services are available. These include guided self-help materials delivered via books, classes and online packages. This project aims to pilot a randomized controlled trial of an online CBT-based life skills course with community-based individuals experiencing low mood and anxiety.

**Methods:**

Individuals with elevated symptoms of depression will be recruited directly from the community via online and newspaper advertisements. Participants will be remotely randomized to receive either immediate access or delayed access to the Living Life to the Full guided online CBT-based life skills package, with telephone or email support provided whilst they use the online intervention. The primary end point will be at 3 months post-randomization, at which point the delayed-access group will be offered the intervention. Levels of depression, anxiety, social functioning and satisfaction will be assessed.

**Discussion:**

This pilot study will test the trial design, and ability to recruit and deliver the intervention. Drop-out rates will be assessed and the completion and acceptability of the package will be investigated. The study will also inform a sample size power calculation for a subsequent substantive randomized controlled trial.

**Trial registration:**

ISRCTN ISRCTN12890709

## Background

Depression is common, with an estimated 350 million people experiencing this mood disorder worldwide [1]. It has a significant impact on health, wellbeing, employment status and social functioning and is the primary cause of disability globally [1]. Various interventions are available for the treatment of depression, such as antidepressant medication and talking therapies, including low-intensity guided self-help interventions as well as high-intensity interventions, often delivered face-to-face, such as individual high-intensity cognitive behavioural therapy (CBT), interpersonal therapy and behavioural activation [2].

However, only between 10 % and 50 % of individuals receive appropriate treatment for their depression within health services [1, 3]. This treatment gap may depend on a number of factors, including non-recognition of the problem (by the individual or healthcare workers), limited knowledge about treatment options and a lack of mental health resources, resulting in long waiting lists. A key aim of the WHO mental health Gap Action Programme is to increase access to psychological therapies via non-expert support or healthcare workers. This could be achieved through the application of a low-intensity CBT guided self-help approach, delivered via bibliotherapy or online in the form of computerized CBT.

Various free and licensed computerized CBT packages are available, including ‘Moodgym’, ‘Beating the Blues’ and ‘Living Life to the Full’ (LLTTF). Studies show varying results regarding effectiveness and adherence to online interventions [4, 5]. A recent meta-review of the effectiveness of computerized CBT for depression found insufficient evidence to indicate which packages achieve better outcomes, indicating a need for further randomized controlled trials (RCTs) of computerized CBT to establish effectiveness [6].

The LLTTF course puts bibliotherapy and life skills training at the centre of the course, providing various ways of completing the course (reading, audiovisual modules, video), presenting a blended learning approach. The resources, which address key aspects of low mood and stress, take the form of classes [7, 8, Williams, McClay, Matthews, Haig, McConnachie, Morrison. A randomosied controlled trial of a community based group guided self-help intervention for low mood and stress. Submitted], printed books [9] and e-books, in addition to the online course. Importantly, the online version of the LLTTF intervention adheres to the key NICE recommendations regarding computerized CBT packages in terms of content, number of modules and the support element provided [2]. A previous non-randomized feasibility study suggests that the online LLTTF course helps improve mood and anxiety; this study compared LLTTF, Beating the Blues and a book-based bibliotherapy intervention, demonstrating equivalent significant improvements across the three interventions [10]. However, further research is needed regarding the efficacy of LLTTF in its online format as to date there have been no adequately powered RCTs of the LLTTF package. Also, following earlier evaluations of LLTTF, the intervention has been refined in three key ways: (1) content has been updated; (2) the delivery platform (website) has been enhanced to add planning and reminder components, alongside the option to read the online linked books and (3) automated support emails as well as a structured support algorithm have been developed [11]. The extent and timing of support is known to improve outcomes in online treatments for depression, with maximal response (a Cohen’s *d* of 0.76) when support is offered both before and during treatment, compared with 0.21 when there is no therapist support before or during treatment, 0.44 when there is therapist contact before treatment, and 0.58 when there is therapist contact during treatment only [12]. We have used the conservative estimate of effect of 0.58 to provide our sample size estimate.

### Aims

In this pilot study, the primary aim will be to investigate take-up, drop-out and completion rates of the online course and the completion rates for data collection.

Secondary outcomes will be mood ratings at 3 months. We will use changes in the Patient Health Questionnaire 9 [13] score to provide data relating to the effect of the intervention on depression levels. This will give an indication of efficacy, together with the drop-out and retention rates.

### Research questions

#### Primary question

Is the study design feasible? Is it possible to recruit from the community, remotely randomize participants, deliver the online intervention with telephone or email support and collect data at baseline and 3 months after randomization?

#### Secondary questions

To what extent will participants demonstrate fidelity to the online intervention?Is the LLTTF online package acceptable to participants?Can we confirm our ability to recruit, and achieve the required sample size in the future substantive study?

## Methods

### Overview

The study will be a parallel, two-arm pilot RCT with a 50:50 allocation ratio across the two groups. Participants will be remotely randomized to receive the online intervention immediately (immediate-access group) or after a 3 month delay following randomization (delayed-access group). The delayed-access group will serve as the control at the primary outcome point. Ethical approval has been granted by the College of Medical, Veterinary and Life Sciences Ethics Committee for Non-Clinical Research Involving Human Subjects, University of Glasgow (Ref. 200140159).

### Participants

#### Procedure for recruitment

People with clinical levels of depressive or anxiety symptoms will be recruited via a number of community-based methods (newspaper advertisements in the *Metro* and local papers, advertisement through the Action on Depression charity, including their websites, a phone support line, newsletters and local groups), supplemented by posters, and options such as Google advertisements. No participants will be recruited directly via the NHS and we will recruit exclusively from the UK. Informed consent will be collected from all potential participants prior to entry into the study.

#### Inclusion criteria

Aged 18 or over.Living in the UK.Ability to understand written and spoken English language.Regular access to a computer, smart phone or tablet with audio and broadband connection.Score of 10 or more on the Patient Health Questionnaire 9.

#### Exclusion criteria

High rating of suicidality (i.e., scoring 2 or 3 on item 9 of the Patient Health Questionnaire 9).Currently receiving any psychological intervention, such as counselling or psychotherapy.New or altered dose of antidepressant in the past month.Taking part in any other research projects.

#### Sample size

We aim to recruit up to 50 participants, consistent with the widely accepted sample size of 30–50 participants for pilot studies [14]. We have taken an estimated effect size of 0.58 to represent a typical response rate to supported or guided online interventions, such as that tested in the proposed study [12]. With a power of 0.58 and a significance level of 0.05, 48 patients per group (total *n* = 96) would be required. Therefore, recruiting 30–50 patients in this pilot trial should be sufficient to enable us to determine whether we can recruit and randomize sufficiently, as well as gauging our ability to retain participants and record follow-up data.

Drop-out rates in internet studies can vary from 1 % to 50 %. We are also planning to record suggested predictors (severity, chronicity and treatment length) [15].

### Randomization

Participants will complete initial questionnaires, and those that are eligible and have consented will then be remotely randomized to either an immediate-access or delayed-access group by the Robertson Centre for Biostatistics. Participants’ ID numbers will be passed to a separate researcher who will use the randomization function in Excel to assign participants remotely to the immediate immediate-access or delayed-access group. As this is a pilot study, we will not stratify for any variables during randomization. The randomization will be done remotely by a researcher who will not be involved in the final data analysis. After randomization, the two groups of participants will be followed up in exactly the same way. Those in the immediate-access group will be given an access code and link to the LLTTF website, including instructions on using the resources. Those in the delayed-access group will be told that they will be contacted again in 3 months; the access code will be sent once follow-up data have been received.

### Intervention

The free-access online LLTTF course consists of eight modules that teach a range of CBT-based life skills.

The eight sessions are as follows:Session 1: ‘Why do I feel so bad?’ – An introduction to the CBT model and the ‘vicious cycle’ of low mood that aims to help participants understand why they feel the way they do and how their thoughts, feelings, physical symptoms and behaviour are linked.Session 2: ‘I can’t be bothered doing anything’ – This module focuses on the impact of reduced activity. Users are encouraged to consider the things that they have stopped or reduced doing as a result of their low mood and make a plan to re-establish these activities in order to improve their mood.Session 3: ‘Why does everything always go wrong?’ teaches skills to help tackle negative thinking, including how to label unhelpful thoughts, identify negative thinking patterns and to turn these thoughts around to create more helpful ones.Session 4: ‘I’m not good enough’ – This session teaches how self-confidence is developed and teaches confidence-building techniques.Session 5: ‘How to fix almost everything’ – A problem-solving approach using an ‘easy four-step plan’ to help break down problems into smaller parts in order to overcome challenges.Session 6: ‘The things you do that mess you up’ – This session addresses unhelpful behaviours that may be worsening mood. Participants are encouraged to recognize problem behaviours such as isolating themselves, or drinking or smoking too much, and then create a plan for reducing them.Session 7: ‘Are you strong enough to keep your temper?’ – Participants learn to recognize the things that cause them to feel irritable or angry and the early warning signs they experience when they start to feel angry. They then learn techniques for better managing their anger to help them react differently to challenging people and situations.Session 8: ‘10 things you can do to feel happier straight away’ – The final module teaches key lifestyle choices that can improve mood, including healthy eating, exercise and closeness with others.

Additional course worksheets, video and audio (relaxation) resources supplement the main modules. These are available on the intervention website.

#### NICE specifications

The NICE guidelines [2] for the treatment of adults with depression advise on the content of online self-help packages. These guidelines state that such interventions should:**Contain age-appropriate written resources** – The LLTTF materials use everyday language and avoid technical CBT terms. Worksheets are colourful and often include illustrations, and can be downloaded free of charge from the website. The linked module books can be either purchased from bookshops or online, or borrowed from many libraries.**Contain six to eight sessions to be completed over 9–12 weeks** – The LLTTF package contains eight sessions, of which the first four sessions are considered the ‘core’ content (formulation, behavioural activation, thinking and confidence, which brings together thinking and behaviour changes).**Have tasks to be completed between sessions (homework)** – A planner and review sheet is used in each module to encourage participants to plan the skills that they will practise or the advice that they will follow in the coming week.**Include thought and behaviour change and monitoring** – The LLTTF package addresses helpful and unhelpful behaviour, increasing activity and a module focused on monitoring and changing unhelpful thinking patterns.**Have a support element, including monitoring and reviewing progress** – Support in the package includes weekly reminders (automated emails) plus support sessions with a support worker delivered weekly via email or telephone. The amount of support time allocated can be varied to reflect the complexity of the needs of the person being supported [16]. The support is protocol driven [11] and focuses on encouraging use and application of the intervention. It is designed to encourage an individualized plan to be made at the end of each session using a ‘plan, do, review’ structure (worksheets are completed), with a focus on participants applying the skills and techniques that they have learned and making changes in their lives; using the materials to support them in doing this. To assess fidelity to the support model in the study, copies of all email supports and recordings of any phone support contacts will be made (with consent) to enable a sample of 20 (5 %) of the support sessions to be evaluated using a previously used adherence and competency checklist [11].

### Risk management

A potential risk to participants is that they might experience an increase in their feelings of low mood or anxiety during the study.

Such risks will be addressed in several ways:Active suicidal risk is included in the exclusion criteria at the screening stage. Once recruited, any participant who is found to have active risk will be signposted to support through a general practitioner, the NHS 111 freephone service or the Samaritans helpline.The study website includes details of sources of urgent help.The trained support workers (staff or volunteers from the Action on Depression charity) are experienced in working with such depressed or anxious people and will be able to assist any individuals who may need additional help during the study by providing information regarding how to access alternative forms of support, and the appropriate action to be taken if the participants feel they need extra help.

### Follow-up data collection

The primary outcome point will be at 3 months after randomization. Given that the focus of this pilot study is on assessing the feasibility of the trial design, no additional follow-up points will be examined. However, depending on the results of this pilot study, progression to a future Phase III definitive RCT will include follow-up to 12 months. This research plan follows Medical Research Council guidance for evaluating complex interventions [17]. In the future substantive study, we will also plan to collect data at 6 months, and possibly one year, to record the sustainability of any improvements. Since the current study is a small pilot study, we are not able to test data collection at these longer time points.

Baseline measures include age, sex, ethnicity, mood, social function, and past and current sources of support. After 3 months, all randomized participants will be invited to repeat mood and social functioning questionnaires. Use of the intervention (using site login statistics) and satisfaction in the immediate-access group will be assessed and the collection of data for an economic analysis will be piloted (these data will not be analyzed). We will also assess contamination regarding other support received and whether anyone in the delayed-access group has accessed the LLTTF course or other similar resources, or otherwise had access to CBT.

### Outcome measures

The key outcomes of the study will be the success of recruitment, retention (a minimum of 75 % follow-up rate), acceptability (as measured by drop-out rates and a standardized questionnaire) and ability to gather data.

The measures used to assess the impact on mood and social functioning, as well as satisfaction with the intervention, are described next.

#### Patient Health Questionnaire 9

This is an open-access mood rating questionnaire consisting of nine questions mirroring DSM-IV depression diagnostic criteria and each rated from 0 to 3, giving a maximum score of 27 [13]. Cut-off scores are used to label depression severity as:0–4, minimal depression5–9, mild depression10–14, moderate depression15–19, moderately severe depression20–27, severe depression

#### Generalized Anxiety Disorder 7

This is a seven-item questionnaire focusing on symptoms of anxiety [18]. Each item is rated according to the frequency of the described problem in the past 2 weeks. The responses are scored as follows: 0 = ‘not at all’, 1 = ‘several days’, 2 = ‘more than half the days’, 3 = ‘nearly every day’. There is a maximum score of 21. Scores of 0–5 on this measure indicate mild anxiety; 6–10, moderate anxiety; 11–15, moderately severe anxiety and 15–21, severe anxiety.

#### Work and Social Adjustment Scale

The Work and Social Adjustment Scale [19] assesses social functioning. It is a five-point questionnaire and addresses issues relating to an individual’s everyday life and functioning and the impact of the individual’s mood disorder on these areas. Responses are given on a scale of 0 to 8, with higher scores indicating a higher level of impairment. Those scoring over 20 are likely to have significant problems in their social functioning.

#### The Client Satisfaction Questionnaire

This is an eight-item questionnaire, rated using a four-point Likert scale [20]. It will be administered after the intervention to the immediate-access group only as a measure of satisfaction. Scores range from 8 to 32, with higher scores indicating greater satisfaction with the intervention in question. The internal consistency of the questionnaire, measured by Cronbach’s *α* coefficient, ranges from 0.83 to 0.93 [20].

### Statistical analysis

Recruitment, uptake and adherence to intervention will be summarized and presented as percentages. Baseline characteristics will be summarized for all participants as well as for the immediate-access and delayed-access groups separately. Two-sample *t* tests or Mann–Whitney tests, depending on distributions, and Fisher’s exact tests will be used to compare the two treatment groups and confirm that participants had been effectively randomized.

To assess efficacy, appropriate linear models will be used, using an intention-to-treat approach. Models will be adjusted for age, sex and antidepressant use at baseline. These models will be used to estimate and test the statistical significance of the within-group change between baseline and 3 months, and the between-group differences at each time point. Rates and characteristics of drop-out will be explored. Progression criteria to a full RCT would be based on adequate recruitment, evidence of possible clinical efficacy and ability to deliver the intervention and collect research data.

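### The claim that 30–50 participants suffice to gauge retention rests on a calculation for a difference in means, and the 75% follow-up minimum is set with no allowance for sampling error

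*Protocol article*

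**What the plan says.** The Aims section makes take-up, drop-out, course completion and data completion the primary interest of the pilot; mood scores are secondary.

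The Sample size section gives two grounds for the number of participants. The first is convention: "We aim to recruit up to 50 participants, consistent with the widely accepted sample size of 30–50 participants for pilot studies". The second follows a calculation of 48 patients per group (96 in total) for an effect size of 0.58: "Therefore, recruiting 30–50 patients in this pilot trial should be sufficient to enable us to determine whether we can recruit and randomize sufficiently". The same sentence extends the claim to follow-up: "as well as gauging our ability to retain participants and record follow-up data".

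The Outcome measures section lists retention among the key outcomes with one number attached: "retention (a minimum of 75 % follow-up rate"). No margin or intermediate range is given.

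The Statistical analysis section says "Recruitment, uptake and adherence to intervention will be summarized and presented as percentages". Drop-out has its own sentence: "Rates and characteristics of drop-out will be explored". Progression is described in words: "Progression criteria to a full RCT would be based on adequate recruitment, evidence of possible clinical efficacy and ability to deliver the intervention", together with being able to gather trial data. The 75% figure does not appear there.

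**The concern.** The number of patients needed to detect a mean difference between two arms does not tell us how precisely a sample of 30–50 estimates a proportion. The step from 96 patients to the sufficiency of 30–50 for gauging retention is therefore unsupported, and the convention for pilot sizes supplies no precision either.

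This matters because the protocol sets a numerical minimum for retention. A team that observes follow-up just above or just below 75% would be told by the Sample size section that the sample was large enough to gauge retention, when the data could not distinguish a design that retains 70% from one that retains 80%. The protocol itself cites drop-out of 1% to 50% in internet studies, that is, retention of 50% to 99%, so true rates near 75% are realistic.

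**Working it through.** **Inputs.** Total n of 30 to 50 (Sample size); minimum follow-up of 75% (Outcome measures); effect size 0.58, significance level 0.05 and 48 per group (Sample size). The true retention rates below are assumptions chosen around the minimum.

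**1. The protocol's own calculation.** For two means, n per group = 2(z₁₋α/₂ + z_power)² / d².
- With 80% power and two-sided 0.05: 2(1.960 + 0.842)² / 0.58² = 46.7, so 47; the t-test version gives 48. This matches the printed 48.
- With the printed power of 0.58: 2(1.960 + 0.202)² / 0.58² = 27.8, so 28 (t-test 29). The printed power therefore does not give 48 and looks like a repeat of the effect size. That is a separate matter and nothing below depends on it.

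No term in this formula is a retention rate or the width of an interval for one.

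**2. Precision for a rate of 75%.** Half-width = 1.96 × √(0.75 × 0.25 / n).
- n = 50: 1.96 × √(0.1875 / 50) = 0.120, about 12 points.
- n = 30: 1.96 × √(0.1875 / 30) = 0.155, about 15 points.

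**3. Intervals at the smallest count that meets 75%.** The count is 0.75n rounded up: 38 of 50, 30 of 40, 23 of 30.

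| Observed | 95% Wilson | 95% exact (Clopper–Pearson) |
|---|---|---|
| 38/50 (76.0%) | 62.6–85.7% | 61.8–86.9% |
| 30/40 (75.0%) | 59.8–85.8% | 58.8–87.3% |
| 23/30 (76.7%) | 59.1–88.2% | 57.7–90.1% |

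Wilson for 38/50: the centre is (0.76 + 3.84/100) / (1 + 3.84/50) = 0.741 and the half-width is 0.116. A rate measured in one arm of 25, such as take-up in the immediate-access group, is looser: 19/25 (76%) has an exact interval of 54.9–90.6%.

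**4. How often the observed rate falls on the wrong side of 75%.** With X ~ Binomial(n, p) and c the count from step 3, the minimum is wrongly met with probability P(X ≥ c) when p < 0.75, and wrongly missed with probability P(X < c) when p ≥ 0.75.

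| True retention | Error | n = 30 | n = 40 | n = 50 |
|---|---|---|---|---|
| 65% | wrongly met | 0.124 | 0.121 | 0.066 |
| 70% | wrongly met | 0.281 | 0.309 | 0.223 |
| 72% | wrongly met | 0.368 | 0.412 | 0.325 |
| 74% | wrongly met | 0.464 | 0.526 | 0.446 |
| 75% | wrongly missed | 0.486 | 0.416 | 0.489 |
| 78% | wrongly missed | 0.333 | 0.252 | 0.296 |
| 80% | wrongly missed | 0.239 | 0.161 | 0.186 |

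Over every n from 30 to 50, the error at 70% runs from 0.206 to 0.344 (mean 0.265) and at 80% from 0.148 to 0.270 (mean 0.200).

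**The case against.** **The missing intervals.** The strongest reply is that this is a condensed article, and that whether a percentage carries an interval is commonly settled in the analysis plan. Reporting percentages does not rule intervals out. That stands: their absence alone would not be a finding. The sentence on percentages also names recruitment, uptake and adherence, not retention, so it cannot be read as fixing how retention is reported. An unseen analysis plan cannot, however, repair an inference that this document itself makes in the Sample size section.

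**The status of 75%.** A reader might infer that the pilot will stop or go on an observed 75%, and that step 4 gives the error rate of the progression decision. The documents do not support this. Progression is described qualitatively, on several criteria, without that figure. The probabilities describe only whether the observed rate meets the minimum in the Outcome measures section.

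**The size of the error.** A reader might also take one in four or five as the error throughout the range within 5 points of 75%. It is roughly the error at 70% and 80%; inside that range it is higher.

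**The modest wording.** The protocol speaks of gauging retention, not of estimating it to a stated precision, and cites a pilot-size convention. That is fair, and it is why the remedy is a correction of wording and not a larger sample.

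**Traffic-light zones.** It may be tempting to replace the cut-off with go, amend and stop zones defined by the interval. If go is kept at an observed 75%, every wrong pass remains. The zones would also depend on the interval method: 31/50 has an upper limit of 74.1% by Wilson and 75.3% by the exact method. I do not recommend this.

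**Conclusion.** The point holds for the sufficiency claim and for the unqualified 75% minimum. The 96-patient calculation does not support the statement that 30–50 participants suffice to gauge retention. At these sizes an observed rate near 75% is uncertain by about 12 points (n = 50) to 15 points (n = 30) either way, so rates of 70% and 80% cannot be told apart. The stated minimum would be wrongly met 22% (n = 50) or 28% (n = 30) of the time at a true 70%, and wrongly missed 19% or 24% of the time at a true 80%, with error near one in two close to 75%.

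These figures assume that participants are followed up independently with a common probability, that retention is counted over both arms, and that the minimum is compared with the observed percentage. The last is the natural reading but is not spelled out. The flaw does not invalidate the pilot; it overstates what the pilot can show on its primary aim.

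**What to change.** - **Sample size:** remove the inference from the 96-patient calculation. State the precision delivered instead: for 75% retention, about ±12 points with 50 participants and about ±15 points with 30. The pilot-size convention can stay as the reason for the number chosen.
- **Statistical analysis:** report each primary feasibility proportion (take-up, completion, and 3-month follow-up overall and by arm) with a 95% interval, by one method named in advance, Wilson or exact.
- **Outcome measures:** say that the 75% minimum will be read together with that interval.

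An interval does not lower the error of comparing an observed rate with 75%; it shows those planning the full trial how far the rate can be trusted. The change needs no further participants or data, only wording and a few calculations. Its downside is that the stated assurance becomes less favourable.

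### Baseline significance tests cannot confirm that randomization worked; describe baseline by arm and check the allocation record instead

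*Protocol article*

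**What the plan says.** The Statistical analysis section of the protocol article first plans a summary of baseline characteristics, overall and by arm. The next sentence adds t or Mann–Whitney tests and Fisher's exact tests, which "will be used to compare the two treatment groups and confirm that participants had been effectively randomized". Given its position, this sentence is about baseline comparisons, and the purpose of the tests is stated outright. No significance level, number of tests or action on a significant result is given for them.

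The same section says that the efficacy models will estimate and test "the between-group differences at each time point". The only time points in the study are baseline and 3 months.

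Other relevant statements:

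- Follow-up data collection: "Baseline measures include age, sex, ethnicity, mood, social function, and past and current sources of support".
- Sample size: "We aim to recruit up to 50 participants", with 30–50 given as the working range.
- Overview: a "50:50 allocation ratio across the two groups".
- Randomization: allocation is remote and unstratified. A separate researcher receives ID numbers and uses Excel's randomization function. The section also names a biostatistics centre as doing the randomizing.
- Statistical analysis: the model covariates are fixed as age, sex and baseline antidepressant use.

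**The concern.** A baseline test between randomized arms asks whether the observed differences are larger than chance would produce. If allocation was properly random, chance is the only source of difference. A small p value is then a false alarm, and with several variables such alarms are common. If allocation was not properly random, the test can reveal it only when the resulting imbalance is large relative to the precision available, and 15 to 25 people per arm give little precision. A non-significant result therefore does not confirm sound allocation, and a significant one does not show a fault.

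At stake is what the pilot report will say about its randomization. On the stated plan it could describe a sound process as suspect, or vouch for a process with a moderate fault, on evidence that supports neither statement.

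**Working it through.** **The plan's own figure.** The article states no figure for the baseline tests. Its only calculated figure is the sample size: "We have taken an estimated effect size of 0.58", then "With a power of 0.58" and "a significance level of 0.05, 48 patients per group". The formula is n per arm = 2(z₀.₉₇₅ + z_power)² / d².

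- Power 0.58 as printed: 2(1.960 + 0.202)² / 0.58² = 27.8, so 28 per arm (29 by the t distribution). This does not reproduce 48.
- Power 0.80: 2(1.960 + 0.842)² / 0.58² = 46.7, so 47 per arm (48 by the t distribution). This does.

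The printed power looks like a repeat of the effect size. That is a separate matter and nothing below depends on it.

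**Inputs for this point.**

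- Arm size: 30–50 participants at 1:1 gives about 15–25 per arm (Sample size; Overview).
- Level: 0.05 two-sided. This is an assumption, because 0.05 appears only in the sample size statement.
- Number of tests, k: assumed to be 5 to 10. Follow-up data collection lists seven items: age, sex, ethnicity, mood, social function, past support and current support. Mood may be tested on both the depression and anxiety questionnaires, and antidepressant use is a further candidate.

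**False alarms under perfect randomization.** For k independent tests, P(at least one p < 0.05) = 1 − 0.95^k.

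| k | 1 − 0.95^k |
|---|---|
| 5 | 1 − 0.774 = 22.6% |
| 7 | 1 − 0.698 = 30.2% |
| 8 | 1 − 0.663 = 33.7% |
| 10 | 1 − 0.599 = 40.1% |

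Independence makes these figures somewhat high. Simulation at 25 per arm, with pairwise correlation of 0.3 and then 0.5, gives about 27% and 23% for seven t tests, and 35% and 29% for ten. Fisher's test is also conservative: at 25 per arm and a prevalence of 30%, its actual error rate is about 2.3%. Four independent t tests plus four such Fisher tests give 1 − 0.95⁴ × 0.977⁴, or about 26%.

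**Detection of a real imbalance.** Power of the two-sample t test comes from the noncentral t distribution with noncentrality d√(n/2) and 2n − 2 degrees of freedom. For d = 0.5 the noncentrality is 0.5√12.5 = 1.77 at 25 per arm and 0.5√7.5 = 1.37 at 15 per arm.

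| True difference (SD) | 25 per arm | 15 per arm |
|---|---|---|
| 0.3 | 18% | 13% |
| 0.5 | 41% | 26% |
| 0.8 | 79% | 56% |
| needed for 80% power | 0.81 SD | 1.06 SD |

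For a binary variable at 30% versus 50%, Fisher's test has power of 23% at 25 per arm and 10% at 15.

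**Steered allocation.** In a simulation with 50 participants, a given share of allocations was steered so that above-median severity went to one arm and below-median to the other. The test on severity detected this as follows:

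- 20% steered (shift about 0.32 SD): detected 20% of the time.
- 30% steered (about 0.48 SD): 40%.
- 50% steered (about 0.79 SD): 83%.

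**The case against.** The strongest reply is that nothing in the trial turns on these p values. That is right. The covariates are fixed in advance, so the tests do not choose the model or bias the efficacy estimate. The key outcomes under Outcome measures are recruitment, retention, acceptability and the gathering of data. The progression criteria rest on recruitment, signs of efficacy, and delivery of the intervention and data collection. None of these refers to baseline balance.

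A reader might still infer that the plan would answer part of its primary question from these tests, since that question includes whether participants can be randomized remotely. The article does not support this. The question is operational, about whether remote allocation can be carried out, and no p value is tied to its answer.

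A reader might also infer that the tests would miss any failure. They would not: at 25 per arm a shift of about 0.8 SD, or steering of half the allocations, would usually be detected. The weakness concerns small and moderate faults. Nor does the article suggest that allocation is being steered. A separate researcher working from ID numbers leaves little evident route for it, and the 0.5 SD shift is only an illustration.

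The reference to each time point could be read as a second check of randomization. That sentence describes the efficacy models, and a baseline contrast may simply be their by-product. It is redundant as an efficacy test, but nothing says that it will be used to judge allocation.

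Finally, baseline testing is common, and much of good practice is already planned: summaries by arm and prespecified adjustment. This narrows the change needed but does not make the stated inference valid.

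**Conclusion.** The point holds, with limited consequence. The article assigns the baseline tests a task they cannot perform. The roughly 23–40% false-alarm figure rests on the assumed 5–10 independent tests at two-sided 0.05, and is somewhat lower under correlation or with Fisher tests. The detection figures of 41% and 26% assume equal arms and a true 0.5 SD shift in a continuous variable. No choice within these ranges turns a non-significant result into confirmation, or a significant one into proof of a fault. The error affects only the statement about the integrity of randomization. Effect estimates, sample size and the progression decision are untouched.

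**What to change.** In the Statistical analysis section:

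- Delete the baseline significance tests and the clause saying that they confirm effective randomization.
- Keep what is already planned: the descriptive baseline summary by arm, and adjustment for the prespecified covariates whatever imbalance is seen.
- Limit the between-group efficacy test to 3 months.
- State that randomization will be verified from the allocation record, for example by comparing each participant's arm with the saved Excel output. The article mentions no list drawn up in advance, so the check should refer to whatever record the allocation step produces. Since the Randomization section names both a biostatistics centre and a separate researcher, say which of them holds it.

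The cost is a text change and fewer analyses. The sample size does not change.
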